##### Objectively measured PA

Triaxial Actigraph GT3X+ accelerometers (Actigraph; Pensacola, FL) will be used to measure PA in a subsample of 400 children. As a triaxial accelerometer, the GT3X captures movement data in three orthogonal directions (vertical, forward-backward and lateral). In line with current recommendations, children will be asked to wear the accelerometer around their waist for at least four consecutive days [50]. The validity of the Actigraph GT3X+ accelerometer as a method of estimating children’s PA has already been assessed [51].

##### Psychosocial variables

The psychosocial variables to be measured are the TPB variables (i.e.*,* attitudes, subjective norms, perceived behavioral control and intentions) and the variables added to the theoretical model underlying the GLMC to fill the intentions-behavior gap (i.e.*,* planning, perception of activity opportunities) (Fig. 3). All 30 questionnaire items have been tested in feasibility studies (details of feasibility testing are given below). Responses to all items are given using a four-point scale: 1 (strongly disagree); 2 (disagree); 3 (agree); 4 (strongly agree).

##### TPB variables

The TPB questionnaire is based on current guidelines [52] and previous TPB research amongst children [29, 31, 32, 53]. Intentions are measured using two items (e.g.*,* ‘Do you intend to engage in PA almost every day of this week?’). Attitudes are measured using six items: three dedicated to the affective component (e.g.*,* ‘Is engaging in PA almost every day fun for you?’) and three to the instrumental component (e.g.*,* ‘Does engaging in PA almost every day improve your physical health?’). Subjective norms are measured using eight items: four items assess the injunctive component (e.g.*,* ‘Would your friends like you to do PA almost every day?’), and four measure the descriptive component (e.g.*,* ‘Does your father engage in PA almost every day?’). Perceived behavioral control is assessed with four items (e.g.*,* ‘Do you think you can do PA almost every day even if you have homework to do?’).

##### Planning and activity opportunities variables

Planning will be measured with five items based on the French version of the Action Planning Scale [54] (e.g.*,* ‘Do you know when you will be engaged in PA during the next week (*e.g., times* of day, day(s) of the week)?’) and perceptions of activity opportunities was measured using five items based on previous studies [29, 43, 55] (e.g.*,* ‘Aside from physical education lessons, do you have opportunities for PA at school, in the playground or in a sports hall?’).

#### Evaluation of parents

##### Shared family PA

Parents will be asked to report their commitment to shared family PA using a questionnaire developed by Rhodes et al. [56] which asks about the frequency and duration of structured and unstructured activities they engage in as a family (i.e.*,* with at least one child) in a typical week. Examples of structured (e.g.*,* parent–child swimming lessons) and unstructured (e.g.*,* family walks) activities are given to clarify these terms. The total duration of parental participation in family PA will then be calculated in hours per week.

##### PA social support

Parental support for children’s PA will be measured with a three-item self-administered questionnaire inspired by the ‘praise and understanding’ subscale of the Parental Involvement In Sports Questionnaire [57] (e.g.*,* ‘I regularly praise my child for all his/her PA’). Responses to items are given using a seven-point scale ranging from (1) strongly disagree to (7) strongly agree.

##### Feasibility studies

Two preliminary pilot studies were conducted to confirm that it is feasible to deliver the GLMC intervention and evaluate the participating children and parents. These studies also represented an opportunity to assess the strengths and weaknesses of the intervention.

The first pilot study was carried out in and involved 306 children aged 7 to 11 years old attending 6 public schools and 104 of their parents. During this study we noted that children found the concept of ‘energy cubes’ very attractive; in fact they became something of a fad. We also found that the format of parents’ meetings (see Module 5, Table 1) were more attractive when they were held at the children’s schools rather than in town halls and organized as ‘round-table discussions about promoting PA’ with teachers, municipal officials and local policy stakeholders rather than organized as ‘PA promotion presentations’.

In 2015 a second study involving 793 children aged 7 to 11 years old from 16 public schools and 329 of their parents was carried out. This pilot study was used to test the feasibility of the evaluation procedure and the potential for recruitment. We found that it was feasible to administer the children’s questionnaires (evaluating self-reported PA, TPB variables and additional psychosocial variables) in a classroom setting (i.e.*,* 50–55 min for the completion of the questionnaire for a class of 20–25 children). We also confirmed the feasibility of the procedure for distributing and retrieving accelerometers from a subsample of children. The parents’ questionnaire was also reported to be feasible. Sixteen of the 53 schools (30%) that were contacted agreed to participate and the rates of return of signed consent forms were 86.7% for the child’s participation in the study, 37% for the wearing of an accelerometer by the child and 33.6% for completion of the parents’ questionnaire.

### Statistical considerations

#### Power analysis

Without considering the clustering effect, it is calculated that 180 children per randomization group are needed to observe a 15% difference in the proportions of children in the intervention and control groups achieving the current internationally recommended level of PA with 80% power, given a two-tailed type I error rate of 5%. We assumed that 35% of children would be achieving the current internationally recommended PA level of 60 min of moderate to vigorous PA per day at baseline.

The clustering structure of the randomization requires a variation inflation factor equal to *1 + (m(1 + cv*^*2*^*)-1)r* [58] where *m* is the mean number of children per cluster; *cv* is a coefficient of variation equal to ratio of the standard deviation of the cluster sizes and *m*; *r* is the intraclass correlation coefficient (ICC) for the communes of one community of communes (i.e.*,* one cluster) and reflects the degree of cluster homogeneity. *r* was set at 0.005 based on preliminary data obtained from pilot studies and the database of ICCs [56] .

Given the number of children in selected community of communes clusters (*m* = 781 children on average; *cv* = 1.05), 3400 subjects are required to observe a 15% difference in the proportion of each group reaching the current international recommendation of 60 min with 80% power. Assuming a loss-to-follow-up rate of 15%, a reasonable estimate of the required sample size is 4000 subjects, i.e.*,* 2000 in the intervention group and 2000 in the control group, corresponding to around 160 classes.

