**Methods:**

This is a two-year cluster-randomized controlled trial comparing an intervention group to a control group, randomized into clusters (community of communes) and stratified by department (Hérault, Gard, Aude) and residential environment (urban, rural). The goal is to recruit 4000 children. The GLMC involves children and their parents, and multiple local grassroots partners, such as school teachers, municipal officials and policy stakeholders. The intervention will be delivered over 3.5 months per year for a two-year period. Pre- and post-intervention, children and parents will be asked to fulfill a questionnaire concerning current PA level, TPB variables (i.e.*,* intentions, attitudes, subjective norms, perceived behavioral control) and other psychosocial variables (e.g.*,* perceptions of activity opportunities). A subsample of 400 children will be proposed to wear an accelerometer (i.e.*,* the Actigraph GT3X+). The primary hypothesis is that the GLMC intervention will increase the proportion of children achieving the World Health Organization’s recommended 60 min of moderate to vigorous PA per day by 15%.

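### The inflation factor uses 781 children per cluster, which with 4000 children implies about 5 communities: 781 is either the wrong input, or the stated 80% power ignores the small number of clusters

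*Protocol article*

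**What the plan says.** The Power analysis section of the protocol article starts from 180 children per arm without clustering. The test is specified as "given a two-tailed type I error rate of 5"%, with 80% power for a 15-point difference, and the baseline is fixed by "We assumed that 35% of children would be achieving the current internationally recommended PA level". The section then applies an inflation factor of 1 + (m(1 + cv²) − 1)r and defines m as the mean number of children in a cluster. The intraclass correlation r "was set at 0.005 based on preliminary data obtained from pilot studies and the database of ICCs [56"]. The result is stated as: "Given the number of children in selected community of communes clusters (*m* = 781 children on average; *cv* = 1.05), 3400 subjects are required". After 15% loss, "a reasonable estimate of the required sample size is 4000 subjects", split 2000 and 2000.

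Under Study design and population, the unit of randomisation is the community of communes, allocated in equal proportions to two arms. All schools in a community form one cluster. The Abstract describes the randomisation as "stratified by department (Hérault, Gard, Aude) and residential environment (urban, rural"), and the Randomization section adds that minimisation is used as well. Schools hear of the study after randomisation, and only willing schools and classes take part.

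**The concern.** In this formula m has to be the number of analysed children per randomised cluster, because that number determines how much the correlation within clusters inflates the variance. If m is 781, the planned total fixes the number of clusters, and that number is very small for a stratified two-arm trial. If the number of communities is larger, 781 cannot be the analysed cluster size.

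The two possibilities have opposite consequences. In one, the planned total is well above what the plan's own formula needs. In the other, the 80% comes from a normal approximation that does not hold with so few clusters. As the section stands, a reader cannot tell which applies, and so cannot rely on the stated power for the primary comparison.

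**Working it through.** **Inputs.** From Power analysis: two-sided alpha 0.05, power 80%, 35% against 50%, 180 per arm, m = 781, cv = 1.05, r = 0.005, loss 15%. From Feasibility studies: 30% of contacted schools agreed and 86.7% of child consent forms were returned. From the Abstract and Study design and population: 1:1 allocation of communities, with 3 × 2 = 6 strata.

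**Reproducing the plan.**
- Comparing 35% with 50% needs 170 per arm without and 183 with continuity correction, so 180 is reasonable. It also shows that the 15% is meant as percentage points.
- Inflation factor: 1 + (781 × (1 + 1.05²) − 1) × 0.005 = 1 + (781 × 2.1025 − 1) × 0.005 = 9.205.
- Total: 2 × 180 × 9.205 = 3314, or 2 × 183 × 9.205 = 3369. Both are within 3% of 3400.
- Loss: 3400/0.85 = 4000.

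**Implied number of clusters.** 4000/781 = 5.1 enrolled and 3400/781 = 4.4 analysed. Both are fewer than the six strata.

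**Reading A: 781 is the eligible population.** The pilot uptake is assumed to carry over to the trial.
- Enrolled per community: 781 × 0.30 × 0.867 ≈ 203. Communities: 4000/203 ≈ 20.
- Factor: 1 + (203 × 2.1025 − 1) × 0.005 ≈ 3.13. Need: 360 × 3.13 ≈ 1130, not 3400.
- For illustration with 12 communities: 3400/12 ≈ 283 analysed per community, factor 3.97, need 360 × 3.97 ≈ 1430.

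These figures keep cv at 1.05. The cv of analysed counts could differ.

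**Reading B: 781 is enrolled children, so about 5 clusters.** Power is taken from a non-central t with clusters − 2 = 3 degrees of freedom, for three values of the non-centrality:

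| Basis | Non-centrality | Power, 3 df |
|---|---|---|
| The value that gives exactly 80% under the normal approximation | 2.80 | 48% |
| 3400 analysed: effective n per arm 1700/9.205 = 184.7 | 2.95 | 52% |
| 4000 analysed: effective n per arm 2000/9.205 = 217.3 | 3.20 | 58% |

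The normal approximation at 3400 gives 83%, which agrees with the plan's 80%. The difference comes from the degrees of freedom.

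**Sensitivity to r, 3400 analysed.** Non-centrality is 0.15/√(0.4775/n_eff), where 0.4775 = 0.35 × 0.65 + 0.50 × 0.50 and n_eff = 1700/factor.

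| r | m = 781, normal | m = 781, t with 3 df | m ≈ 203, t with 18 df |
|---|---|---|---|
| 0.005 | 83% | 52% | above 99% |
| 0.01 | 56% | 32% | about 96% |
| 0.02 | 33% | 19% | about 78% |

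For the last column the factors are 3.13, 5.26 and 9.52. They give n_eff of about 543, 323 and 179 and non-centralities of about 5.06, 3.90 and 2.90.

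**The case against.** The strongest reply is that nothing is miscalculated and that the trial is probably safe. Much of this stands. The figures 3400 and 4000 follow from the stated inputs. The sentence that introduces 781 speaks of children in selected communities, and schools are recruited only after randomisation. Enrolled counts were therefore unlikely to be known when m and cv were set, and the eligible-population reading is the more plausible one. On that reading the error is conservative.

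A reader might infer from 4000/781 that the trial has five communities and is badly underpowered. The documents do not show this. It follows only if 781 is enrolled children, and the number of communities may appear in the design figures, which were not available here, or in the full protocol. A reader might also infer that six strata and two arms require at least 12 communities. That does not follow either: the Randomization section combines stratification with minimisation, and no passage promises a community per arm in every stratum. An argument from the smallest p-value that a re-randomisation test could reach would concern a test the plan does not propose.

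The t-based figures are themselves approximate. The plan analyses the primary endpoint with a longitudinal mixed model with a logit link, and clusters − 2 degrees of freedom with equal arms is a simplification. With an odd number of clusters and cv = 1.05, actual balance would be worse.

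None of this reconciles m = 781 with N = 4000 and the stratified 1:1 design. Under the benign reading, m is still the wrong input by the protocol's own definition.

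**Conclusion.** The point holds as an inconsistency in an input, not as an arithmetic slip. As written, one of two published figures cannot stand. If 781 is the eligible population, the factor of 9.2 and the total of 3400 are overstated, and the formula needs about 1130 to 1430 at roughly 200 to 283 children per community. If 781 is enrolled children, the 80% power is nearer 48% to 58% with about 5 clusters.

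The first range rests on pilot uptake carrying over, or on an illustrative 12 communities, with cv unchanged. The second rests on a t approximation with 3 degrees of freedom. The first reading is more likely, and under it 3400 analysed children keep ample power at r = 0.005 and about 78% at r = 0.02. Separately, the reference number given for the database of intraclass correlations is the one cited under Shared family PA for the parents' questionnaire. That is a minor clerical matter with no effect on power.

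**What to change.** In Power analysis:

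1. State whether 781 counts eligible or analysed children per community.
2. Recompute the inflation factor with the expected analysed children per community and the cv of those counts.
3. Restate the power of the planned 4000 children (3400 analysed), using degrees of freedom based on the number of communities and giving that number beside the result. Show it at r = 0.005, 0.01 and 0.02.
4. Correct the reference for the database of intraclass correlations.

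The cost is a recalculation and a few sentences. The stated power or required size will change, but no extra children are needed.

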#### Statistical analysis

Data will be analyzed on an intention-to-treat basis using Stata software (version 13, StataCorp, College Station, USA). All the statistical tests will be two-sided and *p*s < 0.05 will be considered significant. The number of included subjects and the enrolment curve, the number of theoretical follow-ups corresponding to the number of included subjects, the number of follow-ups actually carried out and the relation between the two will be presented by the randomization group. The cumulated follow-up duration will be calculated and the actual cumulated follow-up duration expected will be presented. The data analysis, carried out on intention to treat will include: (a) the comparison of the enrolment groups (for both the children and the children characteristics), (b) the analyses described below, (c) the missing data sensitivity analysis to determine the statistical nature of the longitudinal data (Missing At Random or Not Missing At Random).

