##### Effectiveness analysis

Baseline similarity of the intervention and control groups will be assessed at cluster level (i.e.*,* communities of communes) and child level using descriptive statistics and *T*-tests or Mann-Whitney tests for continuous variables and χ^2^ or Fisher’s exact tests for categorical variables.

Linear mixed models will be used to determine the impact of the intervention impact; this will allow us to calculate fixed effects, such as the effect of randomization group, and random effects such as the effect of subjects and clusters given the potential for intraclass correlations (between and within subjects and clusters). Longitudinal analysis of the dichotomous primary endpoint (i.e.*,* achieving or not achieving the current internationally recommended PA level of 60 min of moderate to vigorous PA per day) will be conducted with a logit link function, effects of subject, group, time and cluster and the time*group interaction will be calculated. The effect of the intervention will be evaluated at child (and parent) level, but also at school, commune and community of communes levels. Potential confounders such as age and sex will be included in the model as covariates.

The same analytical approach will be applied to the secondary outcome variables. The effect of the intervention on TPB variables and other psychosocial continuous variables will be assessed using similar linear mixed models, with a regress link function.

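### The missing-data sensitivity analysis is given the aim of determining whether data are MAR or NMAR, which observed data cannot show; it should test robustness to departures from MAR instead

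*Protocol article*

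**What the plan says.** The Statistical analysis section commits to intention to treat ("Data will be analyzed on an intention-to-treat basis using Stata software") and names three components. The third is "the missing data sensitivity analysis to determine the statistical nature of the longitudinal data (Missing At Random or Not Missing At Random"). No method is given for it, and no rule says what follows from either answer.

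Under Effectiveness analysis, the longitudinal analysis of the dichotomous primary endpoint "will be conducted with a logit link function, effects of subject, group, time and cluster and the time*group interaction will be calculated". Fitted by likelihood, such a model is valid when missingness is MAR given the outcomes and covariates in the model.

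The Power analysis section gives the expected amount of missing data: "Assuming a loss-to-follow-up rate of 15"%, with no split by arm. The Statistical analysis section also says that expected and completed follow-ups will be reported by randomization group.

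**The concern.** The sentence states both an analysis and its purpose, and the purpose is unattainable. Under MAR, missingness depends only on observed data. Under NMAR, it still depends on the unseen values after conditioning on what was observed. For any NMAR model there is an MAR model that fits the observed data equally well. Observed data can give evidence against data being missing completely at random, but they cannot choose between MAR and NMAR without assumptions that are themselves untestable.

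The sentence also reverses the role of a sensitivity analysis. Such an analysis varies the untestable assumption and asks whether the conclusion survives; it does not classify the data. What is at stake is the reading of the T3 result. If the step ended in a label, the label would be unfounded and could not be used to vouch for the mixed model. Outcome-related loss that differs by arm is possible here, because schools and teachers are told their allocation and controls receive no intervention (Study design and population). The document gives no data on whether it will occur.

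**Working it through.** **Inputs (Power analysis section).**
- Loss to follow-up is 15%. I assume it is equal in the two arms.
- The rate meeting the guideline is 35% ("We assumed that 35% of children would be achieving the current internationally recommended PA level"). That figure is for baseline; I assume it also holds for controls at T3.
- The difference is 15 percentage points, so 50% under intervention.
- Alpha is 5% two-sided ("given a two-tailed type I error rate of 5") and power is 80%.
- Mean cluster size is 781 and the coefficient of variation is 1.05. The intraclass correlation "was set at 0.005 based on preliminary data obtained from pilot studies" and an ICC database.

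**Reproducing the plan's own figures.**
- The plan says "180 children per randomization group are needed to observe a 15% difference in the proportions of children". For 35% v 50%, the standard two-proportion formula gives 170 per arm without and 183 with continuity correction, so 180 is reproduced within 3%. A relative 15% increase (35% to 40.25%) would need 1336 or more per arm, so percentage points are meant.
- Inflation factor: 1 + (781 × (1 + 1.05²) − 1) × 0.005 = 9.205.
- Total: 2 × 180 × 9.205 = 3314, or 2 × 183 × 9.205 = 3369, against the stated 3400.
- Loss: 3400 / 0.85 = 4000, that is 2000 per arm enrolled and 1700 per arm analysed.

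**What the observed data leave open.** In each arm, true rate = 0.85 × observed rate + 0.15 × rate among the missing. Any rate from 0 to 100% among the missing fits the same observed data.
- Intervention: 0.85 × 50% = 42.5%, up to 57.5%.
- Control: 0.85 × 35% = 29.75%, up to 44.75%.
- Difference: from 42.5 − 44.75 = −2.25 points to 57.5 − 29.75 = +27.75 points.

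These are extremes, and they are 30 points wide in any trial with 15% missing per arm. They show only that the data do not identify the answer, not how large the bias is likely to be. Earlier visits sharpen the MAR prediction, but the same argument applies within every observed history.

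**How far from MAR the result would have to be.**
- SE = √((0.50 × 0.50 + 0.35 × 0.65) × 9.205 / 1700) = √(0.4775 × 9.205 / 1700) = 0.0508.
- Smallest significant difference: 1.96 × 0.0508 = 0.0997, about 10 points.
- If only the missing intervention children fall short of the MAR prediction, by a shift δ, the difference becomes observed − 0.15 × δ. Significance is lost at δ = (observed − 0.0997) / 0.15.

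| Observed difference | Shift δ at which significance is lost |
|---|---|
| 15 points | 0.336, about 34 points |
| 12 points | 0.136, about 14 points |
| 11 points | 0.069, about 7 points |

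**Missing intervention children take the control rate.** The intervention rate becomes 0.85 × 50% + 0.15 × 35% = 47.75%. The difference is 12.75 points and z = 12.75 / 5.08 = 2.5, still significant. In general this scenario multiplies the observed difference by 0.85, so significance is lost for observed differences below about 9.97 / 0.85 = 11.7 points.

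The SE is for a crude comparison of two proportions, takes the protocol's inflation factor as given, and is held fixed as δ changes. The planned mixed logit model would give somewhat different figures.

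**The case against.** The strongest reply is that this is loose wording in a condensed article. The step is called a sensitivity analysis and names NMAR, so a full analysis plan may contain genuine NMAR scenarios under that label. This stands as a limit on what can be concluded about the content of the analysis. It does not rescue the stated aim, because no method serving that aim could succeed.

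A reader might go further and infer several things that the document does not support:
- *That the plan gives no protection against informative loss.* The mixed model covers loss that is MAR given earlier outcomes and covariates, and the content of step (c) is not described.
- *That step (c) is the only planned check.* Follow-up expected and achieved is to be reported by arm, which would reveal differential loss, although it cannot test NMAR.
- *That the step will return a MAR label and the model will then be treated as confirmed.* No decision rule is stated.
- *That the primary outcome is self-reported.* The article describes both a questionnaire and accelerometry in a subsample of 400, and does not name the instrument for the primary endpoint.

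It is also fair to say that the planned effect is fairly robust. To overturn 15 points, the missing intervention children would have to meet the guideline at about 50 − 34 = 16%, less than half the assumed control rate. The 11- and 12-point cases are not planned effects; they look fragile because they lie just above the 10-point significance threshold. Finally, delta adjustment is one acceptable method among several, and its fine detail can sit in the analysis plan.

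**Conclusion.** The point holds for the stated aim: the sensitivity analysis cannot determine whether the data are MAR or NMAR, and any such label would not support the primary model's MAR assumption. That conclusion rests on the definitions and needs no numerical assumption.

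The consequence for the T3 result is conditional. With equal 15% loss, informative loss in the intervention arm only and an SE near 5.1 points, an observed 15-point effect withstands all but strongly informative loss. An observed effect of 11 or 12 points could be overturned by shifts of about 7 or 14 points. The document does not show how informative the loss will be. The change should be made because it is cheap and the present sentence is wrong, not because the planned effect is shown to be at serious risk.

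**What to change.** In the Statistical analysis section:
1. Delete the aim of determining whether the data are MAR or NMAR.
2. State that the primary mixed model assumes MAR given the outcomes and covariates it contains.
3. Define component (c) as a check of robustness to departures from MAR for the T3 primary endpoint. Use a prespecified arm-specific delta-adjusted or tipping-point analysis that respects clustering by community of communes. Include one scenario in which missing intervention children take the control-arm rate, and report the shift at which the conclusion changes.

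The size of the steps can be left to the analysis plan; a range of 0 to 40 points would include the 34-point value found above. The cost is one sentence and a few extra model runs, with no new data.
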